## Abstract

**Background::**

Mild neurocognitive disorder (MND) is an intermediate state that can progress to dementia, and the cognitive reserve of MND is an important task in preventing dementia. Acupuncture and neurofeedback (NF) training have been used to improve cognitive function and treat MND or dementia, but their effectiveness remains controversial. In this trial, we will evaluate the efficacy and safety of combined NF-acupuncture treatment in comparison with single acupuncture treatment.

**Methods and design::**

This study is a randomized, assessor-blind, pilot trial. It is designed in accordance with the Standards for Reporting Interventions in Controlled Trials of Acupuncture. A total of 44 MND participants who meet the inclusion and exclusion criteria will be enrolled, and each will be randomly assigned to 1 of 2 groups of 22 subjects. Each subject will visit 24 times over 12 weeks and receive either acupuncture or NF-acupuncture combined treatment. At visit 25 (week 13), a follow-up evaluation will be performed, and then the investigator will analyze the results. The primary outcome is defined by the Korean version of the Montreal Cognitive Assessment score from screening to visit 25. The secondary outcome includes the following: change in Alzheimer Disease Assessment Scale–Cognitive, the Korean version of the Beck Depression Inventory, Body Awareness Questionnaire, delayed matching to sample task scores, and functional near-infrared spectroscopy values, from visit 1 to visit 25; heart rate variability values from visit 1 to visit 5, visit 9, visit 13, visit 21, visit 25; breath per minute values from visit 1 to visit 1 to 25.

**Discussion::**

We will evaluate the effectiveness and safety of combined NF-acupuncture therapy, and expect that it will serve as the basis for the use of NF together with acupuncture in the clinical setting.

**Trial registration number::**

KCT0004972 (registered in Clinical Research Information Service of the Republic of Korea, https://cris.nih.go.kr/cris/search/detailSearch.do/16239)

## Introduction

1

Dementia is a neurodegenerative disorder defined as chronic acquired loss of 2 or more cognitive abilities that represent a decline from the prior level of function, resulting in impaired functional abilities in day-to-day life.^[1]^ According to the World Health Organization, worldwide dementia costs were estimated at US$ 818 billion in 2015, and by 2030, it is estimated that the cost of caring for people with dementia will rise to US$ 2 trillion.^[2]^

Mild neurocognitive disorder (MND) is considered an intermediate state between healthy aging and early dementia, or as a potential state that represents a higher risk of dementia.^[3]^ In South Korea, the prevalence rate of MND is 23.7% in people older than 65 years.^[4]^ To date, there have been no drug interventions that delay conversion to dementia. To prevent progression to dementia in MND, various interventions are needed that include decreasing neuropathological damage and maximizing function.^[3]^

To increase and maintain the cognitive reserve, several cognitive training programs have been increasingly used in MND.^[5]^ An increasing number of studies that present complementary and alternative approaches of acupuncture intervention for cognitive reserves have also been reported.^[6,7]^ The afferent neural circuit of somatosensory induced by acupuncture specifically increase cognitive-related functions.^[8]^ Altered brain function and functional networks of cognitive-related brain regions as well as sensorimotor areas following acupuncture in patients with cognitive impairment support the central nervous system mechanism of acupuncture.^[9–11]^

Neurofeedback (NF) training is a noninvasive brain stimulation technique with operant conditioning closed-loop feedback control mechanism, used in the treatment of a range of neurological and psychiatric conditions.^[12]^ Several studies have reported the effectiveness of NF training in improving cognitive function in dementia^[13,14]^ and MND^[15–17]^ patients.

Based on these neural-neurofunctional groundworks, we believe that combined NF-acupuncture treatment could be a meaningful approach to effectively improve cognitive function. However, due to the lack of clinical research, we plan to conduct a randomized, assessor-blind pilot study.

## Methods

2

### Objectives

2.1

The main objective of this pilot study is to evaluate the efficacy and safety of NF-acupuncture combined therapy compared to acupuncture single treatment in MND patients.

### Study design and setting

2.2

This study is designed as a randomized, assessor-blind, parallel trial. The clinical trial site will be set as Daejeon Korean Medicine Hospital of Daejeon University in the Republic of Korea. The number of eligible participants will be set as 44. Subjects will be divided into 2 equal groups: the combined treatment group (experimental group) and the single treatment group (control group). Each group will be treated twice a week for 12 weeks (visits 1–24). After visit 24, during the follow-up period, participants will be guided to visit for follow-up assessment, which will be visit 25. The primary outcome is the Korean version of Montreal Cognitive Assessment (MoCA-K)^[18]^ score. The secondary outcomes include Alzheimer Disease Assessment Scale–Cognitive (ADAS-Cog)^[19]^ subscale scores, the Korean version of Beck Depression Inventory (K-BDI)^[20]^ score, Body Awareness Questionnaire (BAQ)^[21]^ score, breath per minute (BPM), heart rate variability (HRV) values measured during NF training,^[22]^ functional near-infrared spectroscopy (fNIRS)^[23]^ value, and delayed matching to sample task (DMTS)^[24]^ score. This protocol (version 1.3, July 31, 2020) follows the Recommendations for Standard Protocol Items: Recommendations for Interventional Trial guidelines. The final approval date of clinical research information service registration is April 28, 2020.

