### Study procedure

2.4

All consenting participants will be subjected to the measurement of vital signs (blood pressure, pulse rate, body temperature), demographic information survey, medical history (past, present, family), physical examination, laboratory tests, and electrocardiogram tests. Eligible participants who meet the inclusion and exclusion criteria will receive a schedule of visits (screening).

At visit 1, the investigator will check the subject's vital signs and test ADAS-cog, K-BDI, BAQ, DMTS (response and accuracy), and fNIRS (Oxy-Hb, deOxy-Hb). The control group will receive acupuncture treatment for 30 minutes, while measuring a simple EEG with NF, and the intervention group will receive acupuncture for a minute while performing the NF training protocol (5 times for 5 minutes, 30–60 seconds of rest between each trial). In the meantime, the investigator will check the subject's BPM and HRV. The investigator will check the subject's adverse reactions and concomitant medications and inform them that cigarettes and caffeine must be avoided 2 hours before the test, as they affect the HRV. From visits 2 to 24, both groups will be treated in the same manner as visit 1, and BPM HRV will be checked in the meantime. The investigator will check the subject's adverse reactions and concomitant medications and inform them in the same manner as on visit 1. At visit 24, the investigator will check the subject's vital signs and test ADAS-cog, K-BDI, BAQ, DMTS (response and accuracy), and fNIRS (Oxy-Hb, deOxy-Hb). Additional visits may be performed at any time if deemed necessary by the investigator's judgment, or following the subject's request. In the event of an unexpected visit, the following tests will be performed: vital signs, checking adverse reactions or concomitant drugs, and laboratory tests. In principle, administration of concomitant drugs will be prohibited during the trial, and when combination therapy may occur, it will be decided whether or not to drop out or exclude at the discretion of the principle investigator (PI). A detailed outline of the schedules is shown in Table 1.

**Table 1 T1:** Schedule of trial visits.

	Study period				
Visit	Screening	1	2 to 24	25	UV
Informed consent	О				
Eligibility screen	О				
Demographic information	О				
Drug history	О				
Medical history	О				
Vital signs	О	О	О	О	О
Laboratory test	О				Δ
EKG	О				Δ
MoCA-K	О			О	
ADAS-cog		О		О	
K-BDI		О		О	
BAQ		О		О	
HRV		О	О	О	

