Breath signal of neurofeadback		О	О		
Delayed matching to sample task		О		О	
fNIRS		О		О	
Combined treatment		О	О		
Single treatment		О	О		
Check adverse effects		О	О	О	О
Check concomitant drugs		О	О	О	О
Education of visit schedule	О	О	О	О	О

ADAS-cog = Alzheimer Disease Assessment Scale–Cognitive Subscale, BAQ = body awareness rating questionnaire, EKG = electrocardiogram, fNIRS = functional near-infrared spectroscopy, HRV = heart rate variability, K-BID = Korean version of Beck Depression Inventory, MoCA-K = Korean version of Montreal Cognitive Assessment, UV = unexpected visit.

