#### NF training method

2.5.2

The intervention group will perform the NF sensorimotor rhythm (SMR) training protocol, whereas the control group will have EEG measured for the 30 minutes of acupuncture treatment.

The ProComp 2 Neurofeedback system (Promp Infiniti 8 channel system, Model NO. BA500, Thought Technology Ltd., Quebec, Canada) will be used in this trial. After cleaning the electrode location with an abrasive conductive gel (Nuprep, Weaver and company, CO) and filling the electrode cups with conductive gel (ten 20 conductive paste, Weaver and Company, CO), an electrode will be placed at the subject's central scalp area according to the international 10/20 system. A reference and ground electrode will be placed on the left and right earlobes, respectively. A 3-electrode location input impedance will be maintained under 5 kΩ.^[26]^

The training session will consist of a 6-minute baseline trial and a 30-minute NF training trial, divided into 6 segments. To determine threshold values, each subject will be measured at baseline SMR wave (12–15 Hz, low beta waves) for 3 minutes with eyes closed and 3 minutes with eyes open. NF training, which is designed to increase threshold SMR values, will be performed 6 times for 5 minutes with 20 to 30 seconds of rest between each trial. BPM and HRV values will also be collected in each trial. The threshold value at each trial is newly set according to the subject's feedback.

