#### Secondary outcomes

2.9.2

ADAS-cog, K-BDI, BAQ, fNIRS, DMTS, BPM, and HRV will be the secondary outcomes. Endpoints will include the change in ADAS-cog, K-BDI, BAQ, DMTS scores, and fNIRS values from visit 1 to visit 25; HRV values from visit 1 to visit 5, 9, 13, 21, and 25; and BMP values from visit 1 to visit 25. As primary outcome, we will use the covariance analysis model that includes each group as a fixed factor, ADAS-cog, K-BDI, BAQ, DMTS scores and HRV, BPM, and fNIRS values as dependent variables, and differences in demographic characteristics as covariates. A paired *t* test or Wilcoxon signed-rank test will be performed on the same participant on the secondary outcome before and after treatment in each group.

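### The HRV and breath-rate endpoints run from an in-session visit 1 value to visit 25, where no treatment and no breath recording are scheduled

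*Protocol article*

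**What the plan says.** Among the secondary outcomes, section 2.2 lists "heart rate variability (HRV) values measured during NF training". Section 2.5.2 separates the arms by what happens in the session: "The intervention group will perform the NF sensorimotor rhythm (SMR) training protocol, whereas the control group will have EEG measured for the 30 minutes". It adds that "BPM and HRV values will also be collected in each trial".

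Section 2.4 places the recording inside the session. At visit 1, after describing what each arm receives, it says "In the meantime, the investigator will check the subject's BPM and HRV". For visits 2 to 24, "both groups will be treated in the same manner as visit 1, and BPM HRV will be checked in the meantime".

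Section 2.9.2 defines HRV endpoints as changes from visit 1 to visits 5, 9, 13, 21 and 25, and the breath endpoint as "BMP values from visit 1 to visit 25" (BMP evidently stands for BPM). The abstract also takes the breath endpoint to visit 25.

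Section 2.2 gives treatment at visits 1 to 24, with visit 25 as follow-up. Table 1 agrees, marking neither treatment at visit 25. Its HRV row is marked at visits 1, 2 to 24 and 25. Its row "Breath signal of neurofeadback" is marked at visits 1 and 2 to 24 only.

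**The concern.** A change endpoint needs a scheduled value at each end, taken under comparable conditions. At visit 25, BPM fails the first requirement and HRV appears to fail the second.

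For BPM, the schedule and the endpoint definition cannot both be followed. Sites working from Table 1 will not record the value that section 2.9.2 analyses.

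For HRV, the visit 1 value is taken while one arm trains and the other does not. Any immediate effect of training on HRV is therefore already in the reference value of one arm only. When the change is taken to a visit without a session, that effect is subtracted from the training arm and from nothing in the control arm. A transient response could then look like a between-arm effect at follow-up, and the last point of the HRV series would mean something different from the four before it.

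**Working it through.** **1. Schedule against endpoint**

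| Measure | Visit 1 | Visits 2–24 | Visit 25 | Endpoint runs to |
|---|---|---|---|---|
| Treatment (Table 1) | yes | yes | no | – |
| HRV (Table 1) | yes, in session (2.4) | yes, in session (2.4) | yes, condition not stated | visit 25 (2.9.2) |
| Breath signal (Table 1) | yes, in session (2.4) | yes, in session (2.4) | not marked | visit 25 (2.9.2, abstract) |

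The BPM endpoint has no scheduled final measurement. The HRV endpoint has one, at a visit with no treatment marked.

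**2. What an acute shift does to HRV contrasts**

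The documents give no size for an acute effect, so let a be the in-session shift due to training in the neurofeedback arm only, and L any lasting effect. Contrasts are neurofeedback minus control.

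- Visit 1 contrast: a.
- Visits 5, 9, 13, 21, in session: L + a. Difference in change: (L + a) - a = L. A constant shift cancels.
- Visit 25, off treatment: L. Difference in change: L - a. With L = 0 this is -a.

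If visit 25 HRV is recorded in a state partly like the session, the error lies between 0 and -a, hence up to -a.

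**3. Baseline-adjusted ANCOVA**

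Adjusting for the visit 1 value subtracts b × a, where b is the within-arm slope of visit 25 on visit 1. With equal SDs, b equals the correlation r, so the bias is -r × a: -0.3a at r = 0.3, -0.5a at r = 0.5 and -0.7a at r = 0.7.

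**4. Illustration of size**

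Assumptions: L = 0, r = 0.5, equal SDs, two-sided 0.05. Section 2.6 gives 44 patients and 10% dropout: 44 × 0.9 / 2 = 19.8, about 20 per arm. The power stated there reproduces with these inputs (effect size 0.8, 20 per arm: 69.3% against the stated 69%), so the sample size is not at issue. Simulation with 20,000 replicates per row:

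| a (SD) | Change score: bias | Change score: false positives | ANCOVA: bias | ANCOVA: false positives |
|---|---|---|---|---|
| 0 | 0 | 5% | 0 | 5% |
| 0.25 | -0.25 | 12% | -0.12 | 7% |
| 0.5 | -0.50 | 34% | -0.25 | 13% |
| 0.8 | -0.80 | 70% | -0.40 | 25% |

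As a check, at r = 0.5 the SD of the change is √(2 × (1 - 0.5)) = 1, so a shift of 0.8 SD should be detected about as often as a true effect of 0.8. The 70% agrees with the 69.3% above. With both values in session, the simulated false-positive rate of the change score stayed at 5% for every a.

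**The case against.** The strongest reply is that the protocol openly defines HRV as an in-session measure. Training or not training is the randomised difference, so comparing physiology between arms during sessions is legitimate. This stands for visits 5 to 21. A reader might infer that all HRV and BPM endpoints confuse acute state with lasting effect. The documents do not support that, because in-session changes cancel a constant shift and can be reported as process measures. The reply does not reach visit 25, where no session is marked.

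Second, the result depends on the model. Section 2.9.2 calls the endpoint a change, but its covariance model names HRV and BPM values as dependent variables, with demographic differences as covariates. If raw follow-up values were modelled with no visit 1 term, visit 25 would carry no such error and visits 5 to 21 would carry a. So a full-size error of -a is not a general result. It belongs to the unadjusted change score, and a is assumed.

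Third, the recording conditions are partly inferred. The article does not say how HRV is taken at visit 25. Section 2.5.2 also describes a 6-minute baseline trial, and collection in each trial might include it. But that trial serves to set the training threshold, is not described for controls, and is not named as the HRV or BPM baseline.

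Fourth, on BPM, a reader might infer that the visit 25 value will be missing for all 44 participants, or that carrying the last observation forward would bring in an acute effect. The first assumes that Table 1 prevails over section 2.9.2, whereas the documents show only a contradiction. On the second, nothing says the imputation rule is meant for an unscheduled measurement. A visit 24 value set against visit 1 would in any case be in-session on both sides.

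**Conclusion.** The point holds at visit 25 and only there. For BPM, Table 1 contradicts section 2.9.2 and the abstract, and as scheduled the endpoint has no final measurement. This needs no assumption. For HRV, the change from visit 1 to visit 25 compares an in-session value with an apparently off-treatment one. Any acute effect a of training then enters an unadjusted between-arm change by up to -a, and a baseline-adjusted ANCOVA by about half of that at a correlation of 0.5. For assumed shifts of 0.25 to 0.8 SD with no lasting effect, false-positive rates would be about 12% to 70% for the change score and 7% to 25% for ANCOVA. If a is zero, there is no error.

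The HRV conclusion rests on reading visit 25 as off-treatment from Table 1. These are two secondary outcomes of a pilot trial, and MoCA-K, the primary outcome, is unaffected. The correction is worth making because it is cheap and because the discussion hopes the trial will lead to further studies.

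**What to change.** 1. Reconcile Table 1 with section 2.9.2 and the abstract for BPM: either end the endpoint at visit 24, or add a breath recording at visit 25 alongside HRV.
2. Do not contrast visit 25 HRV, or any visit 25 BPM, with the in-session visit 1 value. Either drop that contrast, or base it on a short no-feedback recording made under the same condition in both arms, before treatment at visit 1 and again at visit 25. State the condition in section 2.9.2.
3. Keep the changes to visits 5, 9, 13 and 21, labelled as in-session process measures.

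The cost is a wording change plus either the loss of one secondary contrast or a few minutes of extra recording at two visits with existing equipment. The visit 1 recording would be new in both arms. Section 2.7 puts needling before training or EEG, so the existing 6-minute baseline trial is apparently made with needles in place and would not serve as a pre-treatment value. Resting recordings at every HRV visit are not needed.

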### Participants

2.3

#### Recruitment

2.3.1

Recruitment will be started on April 22, 2020 (the anticipated date of first enrollment is May 15, 2020, and completed by November 30, 2021. The recruitment period may be extended depending on registration. A consent document that contains information about the background, purpose, intervention, outcome, benefit, and adverse events will be given to all participants or their surrogates. The investigating doctor will explain the consent fully before registration and notify all subjects about the option to withdraw without any penalty.

#### Screening

2.3.2

Subjects who have received sufficient explanation and voluntarily signed the consent form will be given a screening number (ie, DJNP-20-01-S010). The investigator will elevate eligibility by applying the inclusion and exclusion criteria, conducting vital sign checks and laboratory tests, taking demographic information and medical history of the subject. The investigator will open the envelope that contains the randomization code and give the subject an identification code containing the stratification number (ie, DJNP-20-01-R1210).

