### Randomization, blinding

2.7

The investigator in charge of randomization, who will not be involved in the trial, will generate the random sequence list using SAS Version 9.4 (SAS Institute. Inc., Cary, NC) program, and each randomized code will be kept in sealed envelopes, to be managed by the PI. For randomized allocation, the stratified block randomization method will be used, for which the stratification factors will be gender and age. This method involves stratification into 4 subgroups, by age and gender: 1 group of 50 to 60 years old individuals and 1 of 61 to 75 years old individuals for each gender. The investigator assigning the randomization code will open the sealed envelope in front of the participants to whom the identification code is assigned. This investigator will record the date of opening, sign the envelope, and store it separately.

In this trial, blinding of the subjects is not possible; assessor blinding will therefore be performed to control for bias. An investigator doctor not involved in randomization will perform acupuncture on subjects before NF training or simple EEG, will be blinded to the type of treatment to be administered, and will subsequently perform an evaluation of the effectiveness and safety.

Blinding breaking should be determined on a case-by-case basis and considered only in serious medical emergencies. If the investigator determines that blinding breaking is necessary, they can contact the PI or sponsor to obtain consent, and subsequently document the breaking procedure.

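### As the text is ordered, the randomization envelope is opened before the visit 1 baselines of five secondary outcomes, so an unblinded participant may know the arm when they are measured

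*Protocol article*

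**What the plan says.** Section 2.3.2 (Screening) runs in sequence: consent, screening number, eligibility check with vital signs and laboratory tests, and then "The investigator will open the envelope that contains the randomization code and give the subject an identification code containing the stratification number".

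Section 2.7 (Randomization, blinding) adds who is present: "The investigator assigning the randomization code will open the sealed envelope in front of the participants to whom the identification code is assigned". On blinding it says: "In this trial, blinding of the subjects is not possible; assessor blinding will therefore be performed to control for bias". The doctor who inserts the needles "will be blinded to the type of treatment to be administered, and will subsequently perform an evaluation of the effectiveness and safety".

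Section 2.4 (Study procedure) closes the screening step: "Eligible participants who meet the inclusion and exclusion criteria will receive a schedule of visits (screening"). A new step then begins at visit 1, where the investigator checks the subject's "vital signs and test ADAS-cog, K-BDI, BAQ, DMTS (response and accuracy), and fNIRS (Oxy-Hb, deOxy-Hb"). The first treatment session follows, and BPM and HRV are recorded during it. Table 1 agrees: MoCA-K is in the screening column, and the other five measures first appear under visit 1. The table has no randomization row.

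Section 2.9.2 (Secondary outcomes) takes visit 1 as the reference: "Endpoints will include the change in ADAS-cog, K-BDI, BAQ, DMTS scores, and fNIRS values from visit 1 to visit 25". It also plans paired before-and-after tests within each group.

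**The concern.** A baseline is free of any influence of allocation only if it is taken before the participant can know the allocation. Here the only placement given for the envelope is in the screening procedure, ahead of the visit 1 tests.

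A participant who has learned at that point that the assignment is combined or single treatment may answer the K-BDI and BAQ differently, or put more or less effort into ADAS-cog and DMTS. If that reaction differs between arms, the visit 1 means differ for a reason other than chance. The difference then passes into the change from visit 1 to visit 25 even when treatment has no effect. The within-group paired tests use the same visit 1 values and take in whatever shift occurred in that group.

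**Working it through.** **1. Order of events**

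| Step | Where stated | When |
|---|---|---|
| MoCA-K (primary baseline, eligibility limit 22 or less) | 2.3.2.1, 2.9.1, Table 1 | Screening |
| Eligibility check, then envelope opened and identification code given | 2.3.2 | Under the Screening heading; no date given |
| Participant present at opening; subjects not blinded | 2.7 | At opening |
| ADAS-cog, K-BDI, BAQ, DMTS, fNIRS first measured | 2.4, Table 1 | Visit 1, before the session |
| HRV and BPM first recorded | 2.4 | During the visit 1 session |

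Read in order, the envelope comes after MoCA-K and before the five visit 1 measures. No section places it after them.

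**2. The plan's own figure**

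Section 2.6 gives 44 patients, 10% dropout, effect size 0.8, two-sided 0.05 and 69% power. With 22 × 0.9 = 19.8, about 20 evaluable per arm, the two-sample t test (38 degrees of freedom, noncentrality 0.8 × √(20/2) = 2.53) has power 69.3%. The stated figure reproduces, so 20 per arm is used below.

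**3. What a shifted baseline would do to a change score**

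Assumptions that are not in the document: equal SD at visit 1 and visit 25, correlation r = 0.6 between them, no true effect, and a shift of b SD between the arms at visit 1 only.

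- Spurious difference in mean change: b SD, in full.
- SD of change: √(2(1 − r)) = √0.8 = 0.894 SD.
- Standardized bias: d = b / 0.894.
- Noncentrality: d × √10. The rejection rate is from the noncentral t with 38 degrees of freedom.

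| b (SD) | d | Rejection rate, nominal 5% |
|---|---|---|
| 0.1 | 0.112 | 6.4% |
| 0.2 | 0.224 | 10.6% |
| 0.3 | 0.335 | 17.9% |

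For r from 0.5 to 0.8 the rates are 6.1% to 7.8% at b = 0.1, 9.5% to 16.4% at b = 0.2, and 15.2% to 31.0% at b = 0.3. At b = 0.05 and r = 0.6 the rate is 5.3%, hardly different from nominal.

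**4. Dependence on the model**

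With the visit 1 score as a covariate, the bias is b × r and the residual SD is √(1 − r²) = 0.8. For b = 0.1, 0.2 and 0.3 the standardized bias is 0.075, 0.150 and 0.225, and the rejection rates are about 5.6%, 7.5% and 10.7% (same t approximation). Adjustment reduces the problem without removing it. The covariates named in 2.9.2 are demographic differences, not the baseline score.

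**The case against.** **The timing is inferred.** No sentence dates the opening, Table 1 has no row for it, and the Screening section covers the whole entry process. Eligibility depends on laboratory results, so the envelope may in practice be opened at the start of visit 1. This stands as a limit on how firmly the point can be put. It does not remove it: opening at the start of visit 1, before the tests, has the same consequence, and the only order the text gives is the unfavourable one.

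**An article condenses.** The exact order may be fixed in the full protocol, which is not shown. If the article were silent, there would be no point to make. It is not silent: it places the step, and the placement is poor.

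**The arm may not be disclosed at opening.** A reader might infer that every participant knows the arm at every secondary baseline. The document does not say so. The envelope holds a code, and participants might learn their arm only when the session begins. What can be said is that the envelope is opened before them, they are not blinded, and nothing delays disclosure until the tests are done.

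**The shift need not enter the analysis.** A reader might also infer that any shift goes straight into the estimated treatment effect. Section 2.9.2 defines the endpoint as change, but its covariance model names the scores as dependent variables. If the visit 25 score is analysed without the visit 1 score, the visit 1 shift does not enter that comparison. The bias reaches the between-group result only if change is analysed or the baseline is a covariate.

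**Assessor blinding.** It limits bias from the rater, but not a change in the participant's own answers or effort.

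**Conclusion.** The point holds as a matter of sequence. As written, allocation precedes the visit 1 baselines of ADAS-cog, K-BDI, BAQ, DMTS and fNIRS, and participants may know their arm when these are measured. The likely effect is greatest for K-BDI and BAQ, plausible for ADAS-cog and DMTS, and probably smaller for fNIRS, which is a physiological measure.

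The size cannot be derived from the document. The figures of about 6%, 11% and 18% for shifts of 0.1, 0.2 and 0.3 SD rest on the assumed shift, the assumed correlation of 0.6 and analysis of change. They show sensitivity and are not evidence that such shifts will occur.

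The primary outcome is not touched, because MoCA-K is needed for eligibility and so comes before the envelope. With only secondary outcomes of a pilot trial concerned, this is an inexpensive improvement and not a threat to the main comparison.

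HRV and BPM are a separate case. Their visit 1 values are recorded during the allocated session, so they are post-allocation values even if the envelope is opened after the other visit 1 tests.

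**What to change.** State in 2.3.2, 2.4 and 2.7 that the envelope is opened at visit 1 only after eligibility is confirmed and the ADAS-cog, K-BDI, BAQ, DMTS and fNIRS baselines are recorded, and before the first session. Add a randomization row to Table 1 at that point.

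Describe the visit 1 HRV and BPM as first-session values, unless they are also read before the envelope is opened. Reordering the envelope alone does not turn them into pre-allocation baselines.

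The cost is one sentence, carried consistently through three sections, and one table row. Moving the envelope needs no extra visit, test or staff. A pre-opening HRV and BPM reading, if chosen, would add a short recording at visit 1.
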